### Secondary outcome

Secondary endpoints are all cause mortality, non-elective hospital admission (number of episodes and duration), falls (number and severity), fractures, quality of life (SF-12v2), the number and types of drugs (total number, number discontinued, number not discontinued despite the recommendation to discontinue, number re-administered for symptom control), adverse event rate, and medication costs over the observation period.

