### Data management and sample size calculation

Sample size calculation is based on binary analysis of the primary endpoint (non-elective hospital admission or death within 2 years). The study sets out to prove superiority regarding the primary endpoint. Garfinkel observed an 18 % absolute risk reduction achieved by prudent reduction of polypharmacy in a non-randomized controlled trial (from 30 % in the control group to 12 % in the intervention group regarding the annual referral rate to acute care facilities) [23]. This corresponds to a relative risk reduction of 60 % regarding this endpoint.

However, considerably smaller reductions than this still represent substantial clinical and economic benefits; therefore, this study is powered to detect a relative risk reduction of 20 %. We expect to recruit healthier patients than Garfinkel and will use non-elective hospital admission (yes/no) instead of referral rate, because it seems less susceptible to bias. In addition, our primary outcome will combine mortality with hospital admission, since there may be trade-off between these. We have been unable to find empirical data on which to estimate the rate of admission and mortality for our population, but in England in 2010 there was an average of approximately one completed consultant episode for every person in the population aged 75 years or older [43]. The primary outcome of dropouts is coded as an ‘event’ in both groups. Therefore, we consider a low estimate to be half the rate observed by Garfinkel [23]: an annual admission and mortality rate of 15 % of control patients; or 30 % in 2 years. Calculations show that in the event of the actual rate being higher than this, the sample size given below is conservative (ie., larger, rather than smaller, than requirement).

A relative risk reduction of 20 % in the intervention group implies a 2-year event rate of 24 % for that group.

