The sample size is calculated according to Hayes et al. [44] for a power of 80 % (1-*β* = 0.8), *α* =5 %, and an assumed intra-cluster correlation coefficient (for similarity in outcomes between patients within GP practices) of no more than 0.01 (derived from an earlier cluster-randomized trial involving GP practices as clusters [45]). Dropouts in both groups will be considered as treatment failures. Further assuming attrition rates of 10 % of patients and 10 % of GP practices over the period of the study, sample sizes required at recruitment are 3542 patients (1771 per arm) across 322 GP practices at a mean of 11 patients per GP practice (Poisson random variation in patient numbers per GP practice is assumed). To operate a practicable number of GP practices and patients per country we are aiming at 325 GP practices (65 per study center) recruiting 3575 patients (11 patients per GP practice). See Additional file 1: Figure S1.

We will record all data in the PRIMA-eDS eCRF and store them in a XML-database in a secure central server provided by Avain technologies (http://www.avaintec.com/?lang=en). To monitor data quality, we will transfer data to the Department of Medical Informatics, Biometry and Epidemiology, Ruhr University, Bochum, Germany, every week throughout the trial. Statistical analyses will only be carried out after the end of the trial, with no interim analysis planned. Upon completion of data collection, Avain technologies will provide a final file for statistical analysis.

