### Statistical analysis

Statistical analyses are elaborated in a prespecified statistical analysis plan. The binary primary outcome will be analyzed following intention-to-treat principles; secondary outcomes per protocol. A suitable generalized mixed model will be used to account for cluster randomization. Additionally, the study center as fixed factor is included to avoid confounding through stratified randomization. A two-sided *α* of 5 % will be used throughout.

The intervention could result in mortality rates differing between the two trial arms, which could bias analyses of other outcomes if simple exclusion were to be applied. If we find evidence for differential mortality, analysis of secondary outcomes will employ appropriate adjustment methods [46].

Besides a per protocol analysis of the primary outcome, further sensitivity analyses will be undertaken to assess the stability of the results to the model specification, including time-to-event and counts of events analyses as well as patient and GP practice covariates found to be unbalanced across the two trial arms. Random imputation methods will be used, to investigate the sensitivity of the chosen method for replacement of missing values for dropouts in the primary endpoint.

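### Adjustment for death in the secondary outcomes should not wait for evidence that mortality differs between the arms

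*Protocol article*

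**What the plan says.** The protocol article, under Statistical analysis, notes that mortality might come to differ between the arms, "which could bias analyses of other outcomes if simple exclusion were to be applied". The next sentence sets the rule: "If we find evidence for differential mortality, analysis of secondary outcomes will employ appropriate adjustment methods". A reference is cited for the methods, and the details are referred to a separate statistical analysis plan. The article does not say what counts as evidence at this step, although the same section states that "A two-sided *α* of 5 % will be used throughout". Nor does it say what is done when no such evidence is found.

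The list under Secondary outcome includes all-cause mortality, "non-elective hospital admission (number of episodes and duration"), falls, fractures, SF-12v2 quality of life, drug numbers, adverse event rate and medication costs.

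The sample size concerns the composite of first non-elective admission or death. The control assumption is "an annual admission and mortality rate of 15 % of control patients; or 30 % in 2 years", and "A relative risk reduction of 20 % in the intervention group implies a 2-year event rate of 24 % for that group". No mortality rate, mortality effect or mortality power appears.

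**The concern.** The rule lets a preliminary comparison of mortality decide how other outcomes are analysed. This is weak on two separate grounds.

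First, failing to find a difference is not evidence that there is none. The trial was sized for a composite that is more frequent than death alone, so a real mortality difference could easily go undetected.

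Second, even equal death rates would not settle the matter. A change in prescribing could prevent deaths in some patients and bring them forward in others, leaving the totals alike and the survivors different. No mortality test, however powerful, can detect that.

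At stake are the outcomes that death cuts short (admission episodes and days, falls, fractures, costs) or leaves undefined (SF-12v2, drug numbers). Deaths are to be expected: patients are 75 or older, take at least eight drugs and are followed for 2 years. The protocol already treats death and admission together in its primary outcome because one may trade off against the other. That reasoning does not lapse when admission is analysed alone and the mortality comparison happens to be non-significant.

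**Working it through.** **1. Reproduce the stated sample size, to confirm the design effect.** Inputs from Data management and sample size calculation: composite rates 30% and 24%, "for a power of 80 % (1-*β* = 0.8), *α* =5" %, intra-cluster correlation 0.01, mean of 11 patients per practice, attrition of 10% of patients and 10% of practices, dropouts coded as events.

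- Combined attrition: 1 − 0.9 × 0.9 = 0.19.
- Rates with dropouts as events: 0.19 + 0.81 × 0.30 = 0.4330; 0.19 + 0.81 × 0.24 = 0.3844.
- n per arm before clustering = [1.96√(2p̄(1−p̄)) + 0.8416√(p₁(1−p₁) + p₂(1−p₂))]² / (p₁−p₂)², with p̄ = 0.4087 and p₁−p₂ = 0.0486. This gives 1605.
- Design effect: 1 + (11 − 1) × 0.01 = 1.10.
- 1605 × 1.10 = 1765.5; divided by 11 and rounded up this is 161 practices per arm, so 322 practices and 3542 patients.

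This matches the protocol. Power for the composite at 1771 per arm is 80.1%.

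**2. Power of a mortality comparison at that size.** The following are assumptions, not protocol figures: control 2-year mortality p; intervention mortality 0.8p, which borrows the 20% reduction stated for the composite; the intra-cluster correlation of 0.01 applied to death; evidence read as two-sided p < 0.05; vital status known for all.

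- Effective n per arm: 1771 / 1.10 = 1610.
- Power = Φ[(d − 1.96·SE₀)/SE₁], where SE₀ = √(2p̄(1−p̄)/n) and SE₁ = √([p₁(1−p₁) + p₂(1−p₂)]/n).
- 10% v 8%: SE₀ = 0.01009, SE₁ = 0.01008, argument 0.023, power 50.9%, missed 49.1%.
- 15% v 12%: SE₀ = 0.01204, SE₁ = 0.01203, argument 0.531, power 70.2%, missed 29.8%.

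The last column of the table keeps only 81% of patients, with a design effect of about 1.09.

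| Control 2-year mortality (assumed) | Missed, all 1771 per arm | Missed, 81% retained |
|---|---|---|
| 5% | 72% | 77% |
| 8% | 58% | 65% |
| 10% | 49% | 57% |
| 12% | 41% | 49% |
| 15% | 30% | 39% |
| 18% | 21% | 29% |
| 20% | 16% | 24% |
| 25% | 8% | 13% |

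**3. Equal mortality, different survivors.** In an illustrative calculation both arms have 15% mortality. Log-odds of death rise by 1.0 per SD of frailty in one arm, and by 0.5 or 0 in the other. Mean survivor frailty is −0.13 SD in the first arm, against −0.07 or 0.00 SD in the second: a gap of 0.06 or 0.13 SD with no mortality difference. With a slope of 0.75 in the second arm the gap is about 0.03 SD.

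**4. A rough size in the simpler case.** If the intervention only adds survivors, these make up 0.02/0.92 = 2.2% of that arm's survivors at 10% v 8%, and 0.03/0.88 = 3.4% at 15% v 12%. If they differ from the rest by an assumed 1 SD, the survivor mean shifts by about 0.02 or 0.03 SD.

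**The case against.** A journal article may leave both the definition of evidence and the adjustment method to the analysis plan, so neither can be held against it here. That stands. What the article does fix is that adjustment follows only from a mortality finding, and this conditionality is the subject of the point.

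The miss rates rest on borrowed figures. The protocol says that it is "this study is powered to detect a relative risk reduction of 20" per cent, but for the composite, and it found no empirical data on admission or mortality in this population. A reader might take 30% to 49% as a property of the trial. The documents do not support that: it holds only for an assumed control mortality of 15% down to 10%, and the range is wide on either side.

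A reader might also infer that analyses of survivors only are planned whenever the mortality comparison is negative. The text does not say so, and it names simple exclusion as a possible source of bias. Admissions, falls and costs can be counted up to death, and a mixed model can use the 8- and 16-month visits of patients who die later.

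Finally, a skipped adjustment is not a measure of harm. The simple case above gives shifts of only 0.02 to 0.03 SD, and the 0.06 to 0.13 SD gap needs frailty to act quite differently on death in the two arms. The effect of the pre-test on error rates has not been calculated. These limits bear on how much the point matters; they do not justify the condition.

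**Conclusion.** The point holds in a limited form. Making adjustment for death depend on evidence of differential mortality is a poor rule, because a negative comparison shows neither equal mortality nor comparable survivors. The second ground needs no power figure. The first is illustrated by a miss rate of about 49% at 10% control mortality and 30% at 15% (72% to 8% over 5% to 25%), given a 20% relative reduction, 1771 per arm, a design effect of 1.10, a two-sided 5% test and complete vital status. The mortality rate and mortality effect are assumptions that the protocol does not supply.

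The resulting bias is not quantified and may be small. The primary composite already contains death and is unaffected. The change is worth making because the protocol itself identifies the problem and the remedy is cheap.

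**What to change.** Delete the condition. State instead that, for every secondary outcome that death truncates or leaves undefined (admission episodes and duration, falls, fractures, SF-12v2, drug numbers, costs), death is accounted for by one prespecified method whatever the mortality comparison shows.

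Examples are follow-up time as an offset with death as a terminal or competing event for event counts, and a joint or while-alive analysis for SF-12v2 and drug numbers. An offset alone corrects for length of exposure, not for informative death. These options answer different questions, so one should be named per outcome; the choice of model can be left to the analysis plan.

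The cost is a change of wording and modest extra analysis work. Deaths are already recorded for the primary outcome, so no new data are needed.

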### Randomization

The unit of randomization will be the GP practice, such that each participating GP and their patients will be randomized to either have use of the PRIMA-eDS tool (intervention), or not (control). This avoids any risk of contamination that would occur if GPs were using the tool with some of their patients but not others. The intended GP practice cluster size is around 11 patients (see sample size calculation). To assure concealment of allocation, each GP practice reports to the Department of Medical Informatics, Biometry and Epidemiology, Ruhr University, Bochum, Germany as soon as patient recruitment has been completed, and is then cluster-randomized by computerized sequence generation. Thus, neither patients nor GPs will know whether they will take part as an intervention or control cluster at the time of recruitment. To avoid over-representation of a single study center in the intervention group, randomization will be stratified by study center.

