### Documentation and monitoring

#### Baseline-examination

Shortly after consent is obtained, the GPs will assess the following parameters and record all data in each patient’s electronic case report form (eCRF):Age, sex, height, weight, systolic and diastolic blood pressureAll drugs with a systemic effectAll diagnosesCurrent symptoms (within last month)Falls within the last 3 months requiring medical attentionCreatinine, blood glucose, alanine aminotransferase (ALT), hemoglobin A1c (HbA1c), platelet count, international normalized ratio (INR), cholesterol, low-density lipoprotein (LDL)-cholesterol, high-density lipoprotein (HDL)-cholesterol, triglycerides, potassium, sodium. With the exception of creatinine level, GPs should not initiate additional laboratory examinations solely for the study due to ethical reasons and to avoid contamination in this pragmatic trial. They should rather enter the latest values available in the health record and include the date of the measurement. If the tool requires a laboratory value for a recommendation, it provides this information to the GP. The GP can then decide whether to perform the laboratory examination or notSmoking behaviorMedical procedures (e.g., stenting, heart valve replacement)Frailty according to the Clinical Frailty Scale [41]Quality of life questionnaire (SF-12v2) to be filled out by the patient [42]. This will be administered by the GP to the patient on paper. The filled out forms will then be sent to the study centre for electronic data entry

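### Covariates beyond study centre enter only sensitivity analyses and are picked by observed imbalance, where a short prognostic list should be fixed in advance for the primary model

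*Protocol article*

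**What the plan says.** All of the analysis text is in the Statistical analysis section of the protocol article.

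- **Primary model.** "A suitable generalized mixed model will be used to account for cluster randomization". The only fixed covariate named is centre: "Additionally, the study center as fixed factor is included to avoid confounding through stratified randomization". This matches the design, since under Randomization "randomization will be stratified by study center" and no other stratification factor is given.
- **Other covariates.** They appear once, in the sentence stating that "further sensitivity analyses will be undertaken to assess the stability of the results to the model specification". The covariates that qualify are "patient and GP practice covariates found to be unbalanced across the two trial arms". The article gives no list and no definition of imbalance.
- **What is available.** The Baseline-examination section lists age, sex, all systemic drugs, diagnoses, falls in the previous 3 months that needed medical attention, and "Frailty according to the Clinical Frailty Scale", among other items.
- **Timing.** Baseline data are to be recorded shortly after consent. Under Randomization, a practice is randomised once it has finished recruiting.

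The article refers to a prespecified statistical analysis plan, which is not available here.

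**The concern.** Practices are allocated by a computer-generated sequence after recruitment closes, so differences between arms in baseline variables recorded before allocation are due to chance. Whether a variable differs between arms says nothing about whether it predicts the outcome. An imbalance rule can therefore admit a variable with no prognostic value and leave out a strong predictor whose difference is smaller. It also makes the adjusted model depend on the data, although the purpose of that analysis is to test how stable the result is to model specification.

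Two things are at stake. First, the primary model gives no planned role to baseline predictors that are collected anyway, so some precision is lost in a trial planned at 80% power. Second, if frailty or age happens to differ between arms, the only planned response is an adjusted model chosen after the difference has been seen, and critics could call it post hoc.

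**Working it through.** **1. Reproduce the planned sample size.** Inputs from the sample size section: 30% against 24% events at 2 years, 80% power, two-sided 5%, intra-cluster correlation 0.01, 11 patients per practice, 10% attrition of patients and 10% of practices, dropouts counted as events.

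- Combined attrition: 1 − 0.9 × 0.9 = 0.19.
- Event rates as analysed: control 0.19 + 0.81 × 0.30 = 0.433; intervention 0.19 + 0.81 × 0.24 = 0.3844; difference 0.0486.
- Variance term: 0.433 × 0.567 + 0.3844 × 0.6156 = 0.4821.
- Design effect: 1 + 10 × 0.01 = 1.10 (1.11 with Poisson-distributed practice sizes).
- Practices per arm: 1 + (1.96 + 0.84)² × (0.4821 / 11) × 1.10 / 0.0486² = 161.2, or 1773 patients. With 1.11 it is 162.7 practices, or 1789 patients.

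The article states 1771 per arm, so its figure reproduces. It already includes the dilution from counting dropouts as events and holds no hidden reserve of power.

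**2. Power without covariates.** The formula adds one practice per arm, so 160 × 11 = 1760 patients carry the information. Effective size is 1760 / 1.10 = 1600 per arm. The standardised effect is 0.0486 / √(0.4821 / 1600) = 2.80, and power is Φ(2.80 − 1.96) = 80%.

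**3. Gain from adjustment.** If covariates explain a share R² of the variance of the analysed outcome, the standardised effect becomes 2.80 / √(1 − R²). The article gives no R², so 5 to 15% among completers is assumed. About 19% of outcomes are set to event by rule. If dropout is unrelated to the covariates, R² shrinks by

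0.81² × (0.27 × 0.73) / (0.409 × 0.591) = 0.54,

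where 0.27 is the mean of 0.30 and 0.24, and 0.409 is the mean of 0.433 and 0.3844.

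| R² among completers | R² as analysed | Power with dilution | Power if dilution is ignored |
|---|---|---|---|
| 0 | 0 | 80% | 80% |
| 5% | 2.7% | 81% | 82% |
| 10% | 5.4% | 82% | 84% |
| 15% | 8.0% | 83% | 86% |

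With design effect 1.11 the figures are lower by about half a point or less.

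**4. Simulation.** This used 322 practices of 11 patients, five prognostic covariates, 19% of outcomes set to event, 1200 runs per setting, and linear regression with cluster-robust errors as a stand-in for the mixed model. Imbalance was defined by a 5% test, which is an assumption.

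- Type I error was 4.2 to 5.2% whether the analysis was unadjusted, adjusted for all five covariates, or adjusted for those found imbalanced.
- Power, at R² as analysed:

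| R² | Unadjusted | Pre-specified | Selected by imbalance |
|---|---|---|---|
| 0.024 | 82.7% | 82.6% | 82.6% |
| 0.051 | 84.1% | 85.6% | 84.4% |
| 0.079 | 82.8% | 84.5% | 83.3% |

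Pre-specified adjustment thus added about 0 to 2 points, and selection by imbalance recovered little of that.

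**The case against.** The strongest reply is that nothing in the primary analysis is wrong. It accounts for clustering and for the only stratification factor, the criticised rule touches only a sensitivity analysis, and the unseen analysis plan may name covariates or define imbalance. Much of this stands. The absence of a list or threshold from an article is not a fault in itself. The selection rule, however, is stated, and an analysis plan faithful to that sentence would still choose covariates by observed imbalance.

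Some stronger inferences are tempting and the article does not support them.

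- **That the primary test is invalid or the estimate biased.** Chance imbalance is already reflected in the standard error, and simulated type I error was close to 5%. Imbalances should also be small: assuming a covariate intra-cluster correlation of 0.01 to 0.10, the standard error of a standardised baseline difference is √(2 × 1.10 / 1771) = 0.035 to √(2 × 2.00 / 1771) = 0.048.
- **That power would rise to 82 to 86%.** This takes 5 to 15% as R² on the analysed outcome and ignores the dropout coding. If the covariates also predict dropout, the gain could exceed the diluted figures, but the article gives no basis for that.
- **That about one variable in 20 will be falsely flagged.** This is correct arithmetic (20 × 0.05 = 1) for a 5% screen of 20 items, but the article states neither a test nor a number of items.
- **That all baseline values precede randomisation.** The Baseline-examination and Randomization sections imply it, but neither says that baseline entry must be complete before allocation is known. GPs are unblinded and score the frailty scale themselves, so this bears on the remedy.

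It is also fair to say that prognostic strength is a clinical judgement here, and that entry at eight or more drugs narrows the range of drug count as a predictor.

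**Conclusion.** The point holds as one of efficiency and pre-specification. The article commits to choosing adjustment covariates by observed imbalance, which selects on chance, and gives baseline predictors no planned place in the primary model. The centre-adjusted primary analysis stays valid.

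The cost is about 1 to 3 points of power (80% against roughly 81 to 83%). That range assumes R² of 5 to 15% among completers, 19% of outcomes coded as events, and dropout unrelated to the covariates; the article supplies only the attrition rates and the coding rule. The change is worth making because it is nearly free and removes an avoidable challenge to the adjusted result.

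**What to change.** 1. Name a short list of baseline covariates as fixed effects alongside centre in the primary mixed model, for example age, sex, number of drugs, Clinical Frailty Scale and falls in the last 3 months.
2. Use only values recorded before the practice's allocation is disclosed, and require baseline entry to be locked by then. This matters most for the GP-scored frailty scale.
3. Report a standardised risk difference or risk ratio, because covariate adjustment changes the conditional odds ratio of a logistic mixed model.
4. Delete the imbalance trigger.
5. Keep the centre-only model as a sensitivity analysis.
6. State in advance how missing values of these covariates are handled.

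The cost is wording in the protocol and analysis plan, plus confirmation of when baseline entry is locked. No new variables are needed. The downside is small: a few missing baseline values to handle and a change in the conditional estimand, which item 3 addresses.
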